## Abstract

**Introduction:**

Inadvertent perioperative hypothermia (IPH) refers to a core body temperature lower than 36.0 °C, which can contribute to many adverse events. The special physiological characteristics in children further increase the incidence of IPH. Therefore, it is very important to perform effective perioperative warming measures for children. Traditional passive warming measures with additional layers have limited thermal insulation effects. Active warming measures might be the better choice, and most measures have achieved good effects in adults. This study combines a variety of active warming measures to propose perioperative active warming strategies and aims to verify the feasibility and thermal insulation effects of perioperative active warming strategies in children.

**Methods:**

This study is a multicentre, prospective, randomized controlled trial. From August 2022 to July 2024, 400 paediatric patients undergoing elective surgery will be recruited in four centres and randomly divided into the active warming strategies group and control group at a ratio of 1:1. The primary outcome is the perioperative cumulative hypothermia effect value (*Σ Δ*Ti × *Δ*ti, i = 1…, *n*). Multiple complications covering the anaesthesia recovery period and postoperative hospitalization will be considered as secondary outcomes to comprehensively analyse the prognosis.

**Trial registration:**

ClinicalTrials.gov identifier: ChiCTR2200062168. Registered on July 26th, 2022. Registered with the name of “Perioperative Active Warming Strategies in Children: A multicenter, prospective, randomized controlled trial”. URL:http://www.chictr.org.cn/showproj.aspx?proj=172778.

## Introduction

1.

Constant core body temperature is a necessary condition to ensure basic metabolism and vital activity, and normal core body temperature is generally between 36.5°C and 37.5°C (1, 2). A perioperative core body temperature lower than 36.0°C is defined as inadvertent perioperative hypothermia (IPH) (3). The incidence of IPH in adults is approximately 50% to 90% (4). IPH can contribute to a variety of perioperative complications (5), such as cardiovascular accidents (6, 7), increased bleeding (8, 9), surgical incision infection (10), delayed recovery (11), internal environment disturbance (12), and prolonged length of stay. Young age is an important risk factor for IPH (13, 14). The special physiological characteristics of children determine that their body temperature is more susceptible to environmental changes (15). Without proper warming measures, the incidence of IPH could be higher than that in adults. The thermoregulation system of children is not mature, including limited hair, less subcutaneous fat, and a greater overall surface area to body weight ratio, and the ATP-based independent thermoregulation mechanism has not been fully established, leading to insufficient heat production and excessive heat dissipation (5, 16). This relationship is especially true for infants, who generate heat through brown adipose tissue metabolism instead of shivering in low-temperature environments. This metabolism is innervated by sympathetic nerves and inhibited during general anaesthesia, further increasing the risk of IPH (17–19). Therefore, it is imperative to undertake appropriate warming measures for children during the perioperative period.

There have been growing concerns about perioperative complications caused by IPH, and passive warming measures have been widely used in perioperative anaesthesia management. However, a single layer of the passive warming measure can only reduce skin heat loss by approximately 30%, and adding additional layers can only barely increase benefits (20). In contrast, active warming strategies are more effective, and the effects have been verified in adult patients (21). Active warming strategies generally include forced-air warming blankets (19, 22), infusion heating apparatuses (23), forced air warmers (24), body cavity lavage liquid heating (25), increasing operating room temperature (26), etc. In addition, some studies have pointed out that prewarming 30–60 min before the operation can effectively decrease the incidence of IPH by reducing the redistribution of core body temperature (27, 28). The aforementioned active warming measures have been partially applied in children's perioperative management (29), but few trials have systematically studied the effects of the series of active warming strategies in children. This multicentre, prospective, randomized controlled trial aims to verify the effect of perioperative active warming strategies in children, further reducing the incidence of IPH and improving the prognosis in paediatric patients.

## Materials and methods

2.

### Trial design

2.1.

This study is a multicentre, prospective, randomized controlled trial that will enrol 400 paediatric patients who meet the inclusion and exclusion criteria. The main research centre is Beijing Tiantan Hospital, Capital Medical University, and three other research centres will be recruited to assist in completing the study. The study schedule is shown in Figure 1, and the patient flow diagram is presented in Figure 2.

**Figure 1 F1:**
[figure not shown]
Study schedule. Group A, active warming strategies; Group C, control group; PACU, postanaesthesia care unit; CAPD, Cornell Assessment of Pediatric Delirium.

**Figure 2 F2:**
[figure not shown]
Patient flow diagram. Group A, active warming strategies; Group C, control group; PACU, postanaesthesia care unit; CAPD, Cornell Assessment of Pediatric Delirium.

### Ethics approval and consent to participate

2.2.

This trial was approved by the Institutional Review Board (IRB) of Beijing Tiantan Hospital, Capital Medical University on July 3rd, 2022 (approval number: KY2022-101-02), and strictly adhered to the principles of the Declaration of Helsinki. All eligible paediatric patients and their legal guardians will be informed of the trial protocol within the period from the first day of hospitalization to the day before the operation and will be given sufficient time to consider whether to participate. The paediatric patients will be formally included in this trial only if their legal guardian (and school-age children) sign the informed consent form, and they will be able to withdraw at any time during the study period.

We also attach great importance to the information security of participants. Each child involved in this trial will be assigned a unique identification code to hide his or her private information after signing the informed consent form, and the code will not be shared outside this study. All paper materials, such as case report forms (CRFs), will be locked in a cabinet of the anaesthesiology department of Beijing Tiantan Hospital, Capital Medical University, and the electronic information will be stored in EpiData software (version 3.1 data entry). Only the principal investigator (PI) and IRB have access to all of the information. The researchers in charge of the results analysis will need to apply for access permission from the PI, and the access time will be recorded in detail.

### Eligibility

2.3.

Children aged 1–12 years old scheduled for elective surgery will be screened for eligibility. The inclusion and exclusion criteria are as follows.

#### Inclusion criteria

2.3.1.

(1)Paediatric patients ≥1 year old and ≤12 years old, no gender limitations;(2)Scheduled for elective non-cardiac and non-transplant surgery under general anaesthesia or general anaesthesia combined with other anaesthesia methods (The specific types of surgery include pediatric general surgery, pediatric neurosurgery, pediatric urological surgery, pediatric otorhinolaryngologic surgery surgery);(3)American Society of Anesthesiologists physical status of I–II;(4)Estimated operation time of >40 min; and(5)Growth according to the normal range of WHO Child Growth Standards.

#### Exclusion criteria

2.3.2.

(1)Abnormal body temperature caused by diseases or medicines before surgery;(2)Elective surgery requiring controlled hypothermia;(3)Children with a definite history of cardiac insufficiency or congenital heart disease;(4)Children with a definite history of metabolic diseases, such as thyroid dysfunction and diabetes;(5)Changes in laboratory examination of routine blood, blood biochemistry, and blood clotting exceeding 1.5 times the normal value;(6)The tracheal tube expected to be retained after the operation;(7)Postoperative thermoregulation expected to be affected, such as the neurosurgery in the vicinity of the hypothalamic thermoregulatory centre; and(8)Unwillingness to participate in this trial or participate in other clinical trials.

#### Dropout criteria

2.3.3.

(1)Necessary postoperative sedation therapy;(2)Retaining of tracheal tube accidentally after operation;(3)Receiving a second operation during hospitalization; and(4)Refusal to continue to participate in the experiment.

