### Randomization and blinding

2.5.

This study applies a randomized stratified block design. According to the number of research centres, it is divided into four strata. In each stratum, the number of blocks is 2, and the length of the blocks is 4. The eligible children will be randomly assigned to Group A and Group C at a ratio of 1:1. The randomization will be completed by SAS software (SAS Institute Inc., USA). The allocation information will be concealed in sealed, opaque envelopes and opened by the anaesthesiologists in charge before the children enter the preoperative waiting room. To ensure the participants' safety and to complete warming measures, the anaesthesiologists in charge will not be blinded, and they will not participate in follow-up or results analysis. In addition, the allocation information will be blinded for patients and the researchers in charge of follow-up. The interim analysis will be completed by researchers independent of the overall trial process.

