#### Secondary outcomes

2.7.2.

(1)Cumulative hypothermia effect value (*Σ Δ*T_i_ × *Δ*t_i_, i = 1…, *n*) in the preoperative waiting room, operating room, and PACU;(2)Difference value between intraoperative core temperature and axillary temperature;(3)Results of arterial blood gas analysis in the anaesthesia recovery period, including pH, lactic acid, and haemoglobin values;(4)Shivering score, Cornell Assessment of Pediatric Delirium score, and thermal comfort score in the anaesthesia recovery period;(5)Body temperature in the morning of the first day after surgery;(6)The incidence of incision infection during hospitalization;(7)The morbidity of major complications during postoperative hospitalization;(8)Length of stay and expenses;(9)All-cause mortality 30 days after the operation.

Note: a. Anaesthesia recovery period refers to the time from stopping anaesthetic infusion to the time when the children are completely conscious and fully awake. b. Major complications during postoperative hospitalization include postoperative pulmonary complications, arrhythmias requiring treatment, myocardial infarction, sepsis, renal failure, central nervous system events, anastomotic leakage, and accidental transfer to the intensive care unit.

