### Sample size calculation

2.8.

This study is a multicentre, prospective, randomized controlled trial. According to the pretest, the mean ± standard deviation of the perioperative cumulative hypothermia effect value (*Σ Δ*T_i_ × *Δ*t_i_, i = 1…, *n*) under passive warming measures is 12.2 ± 4.31, and using perioperative active warming strategies, it can be decreased by 15%. Considering a dropout rate of 20%, 400 subjects will be required with 90% power and an *α* level of 0.05. The sample ratios of the four centres are *Q*_1 _= *Q*_2 _= *Q*_3_= *Q*_4 _= 1/4N = 100.

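### Section 2.3.3 treats three postoperative events as dropout, although warming may influence them and they are closely tied to the secondary outcomes

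*Protocol article*

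**What the plan says.** Section 2.3.3 gives four dropout criteria. Three are clinical events: "1)Necessary postoperative sedation therapy;(2)Retaining of tracheal tube accidentally after operation;(3)Receiving a second operation during hospitalization". The fourth is a true withdrawal: "Refusal to continue to participate in the experiment". The section does not distinguish between them.

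Section 2.5 fixes the time of allocation. The envelopes are "opened by the anaesthesiologists in charge before the children enter the preoperative waiting room", so criteria (1) to (3) can only be met after randomisation. The same section says that "the anaesthesiologists in charge will not be blinded".

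Section 2.8 sizes the trial with "Considering a dropout rate of 20" per cent and does not divide that allowance among the four criteria.

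The Introduction says that hypothermia contributes to increased bleeding and to "surgical incision infection (10), delayed recovery (11), internal environment disturbance (12), and prolonged length of stay". Section 2.7.2 counts incision infection, a set of major complications that ends with "anastomotic leakage, and accidental transfer to the intensive care unit", length of stay, a delirium score and 30-day mortality. Section 2.7.3 plans follow-up during the hospital stay and at day 30. It does not say whether a child who meets a dropout criterion stays in.

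**The concern.** A dropout criterion should describe a family that leaves the trial, not a clinical course that the treatment may alter. Bleeding, infection and delayed recovery are plausible routes to a second operation, a retained tube or sedation. A reoperation for a leak or infection meets criterion (3), and an unplanned retained tube followed by intensive care meets criterion (2). The children with the most severe postoperative course are then the likeliest to go.

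Randomisation protects the comparison only while the children compared are those randomised. If removal depends on both arm and prognosis, the remaining groups differ for reasons other than warming. The complication outcomes are the most exposed, because a few lost cases can change a low rate. The primary value accumulates over the waiting room, the operating room and the PACU, and a second operation normally comes later. Criterion (3) therefore gives no reason to discard that value.

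If dropout also ends follow-up, no later choice of analysis set can recover infections, complications or day-30 status that were never collected.

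**Working it through.** **Inputs.** Section 2.8 gives a control mean of 12.2, SD 4.31, a 15% reduction (0.15 × 12.2 = 1.83), 20% dropout, 90% power, α 0.05 and N = 400. Allocation is 1:1, so 200 per arm. Two-sided testing is assumed. The documents give no rate for criteria (1) to (3) in either arm, so the removal rates below are assumptions.

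**The plan's own figure.** Per arm, n = 2 × (1.960 + 1.282)² × (4.31/1.83)² ≈ 116.6, so 117. The total is 234, and 234/0.8 = 292.5, so 293. The stated 400 is not reproduced. That is a separate matter, it errs on the generous side, and nothing below depends on it.

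**Does keeping the children cost power?** Power ≈ Φ(1.83/SE − 1.960), with SE = 4.31 × √(2/n).
- All kept, n = 200: SE = 0.431, power 0.989.
- 20% removed from each arm without selection, n = 160: SE = 0.482, power 0.967.

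Keeping them costs no power.

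**Illustrative bias in the primary outcome.** Let pC and pA be the proportions removed from control and Group A, and let removed children average k SD above their own arm mean. The retained mean of an arm falls by p/(1 − p) × k × 4.31, so the bias in (control − active) is

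−[pC/(1 − pC) − pA/(1 − pA)] × k × 4.31.

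For 10% v 5%: 0.1111 − 0.0526 = 0.0585. Multiplied by 4.31 this is 0.252 at k = 1, and 0.126 at k = 0.5.

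| Removed, control v active | k | Bias | Share of 1.83 | Retained difference | Power | Type I error if no true effect |
|---|---|---|---|---|---|---|
| 10% v 10% | 0.5 or 1 | 0 | 0% | 1.83 | 0.981 | 0.050 |
| 10% v 5% | 0.5 | −0.13 | 7% | 1.70 | 0.967 | 0.059 |
| 10% v 5% | 1 | −0.25 | 14% | 1.58 | 0.941 | 0.087 |
| 20% v 10% | 0.5 | −0.30 | 16% | 1.53 | 0.905 | 0.098 |
| 20% v 10% | 1 | −0.60 | 33% | 1.23 | 0.748 | 0.248 |
| 10% v 20% | 0.5 | +0.30 | 16% | 2.13 | 0.995 | 0.098 |
| 10% v 20% | 1 | +0.60 | 33% | 2.43 | 0.999 | 0.248 |

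The sign follows the arm that loses more children. If controls lose more, the benefit is understated; if Group A loses more, it is overstated.

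**Worst case.** If the removed children were exactly the coldest tail of a normal outcome, each arm mean would fall by φ(z)/(1 − p) × 4.31. The differences between arms are then 0.255 for 5% v 2% (14% of 1.83), 0.373 for 10% v 5% (20%) and 0.668 for 20% v 10% (36%). These are upper-end figures, because they require removal to follow the primary outcome perfectly.

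**Complication outcomes.** No rates are given, so no figure can be computed. A removed case leaves both numerator and denominator. Because these children are disproportionately likely to have a complication, the observed rate in that arm falls.

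**The case against.** The strongest reply is that the article never says that dropouts are excluded from analysis. It condenses a fuller protocol, the analysis set may be defined elsewhere, and section 2.7.3 plans follow-up without naming an exception. It is therefore too much to infer that the article states outright that a reoperated child is removed from the complication counts. What stands against the reply is the rule as printed: clinical events carry the same label as refusal, the sample is enlarged for that label, and nothing says that these children remain. The point is about that rule and not about a missing analysis set.

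A reader might also infer that up to 80 children (0.20 × 400) are at stake. The documents do not support this, because the allowance covers refusal too and is not an estimate for criteria (1) to (3). Nor do they support a bias of 20% or more as the expected size, since that needs the worst-case tail or high removal rates. The population is elective and ASA I–II, expected tube retention is already an exclusion, and section 2.4 requires active warming below 35°C in both groups, which limits extreme values. The events may be few.

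Sedation, a retained tube and a second operation are not themselves listed secondary outcomes. The Introduction links hypothermia to bleeding, infection and delayed recovery, and the further step to these three events is clinical inference. The link is plausible, but it is not stated.

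Finally, completeness of the primary value is clear for a second operation and less so for criteria (1) and (2). Section 2.6 sends children to the PACU after extubation, so a child with a retained tube may have no PACU segment. This calls for care in handling the missing segment and does not justify removing the child.

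**Conclusion.** The point holds as a defect in a stated rule. Section 2.3.3 classes three post-randomisation clinical events as dropout, and with section 2.8 the natural reading is that these children are lost to follow-up and analysis. Removal can bias the comparison, chiefly for the complication outcomes, and criterion (3) discards primary values that are normally complete.

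Size and direction are unknown. With 10% v 5% removal and removed children 0.5 to 1 SD above their arm mean, the primary difference shifts by 0.13 to 0.25, or 7% to 14% of 1.83, and power stays above the planned 90%. Larger shifts need higher removal rates or worst-case tail removal. With equal and equally selective removal the bias is zero. All these figures rest on assumed rates, SD 4.31 in both arms and a normal approximation. That the loss is greater for complications than for the primary outcome is a reasoned expectation and has not been computed.

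**What to change.** - In section 2.3.3, limit dropout to withdrawal of consent, and keep data collected before withdrawal.
- State that children who meet criteria (1) to (3) stay in follow-up to day 30, and that all randomised children are analysed in their assigned group.
- Report sedation, retained tube and second operation by arm.
- Run the present exclusions only as a sensitivity analysis.
- For a child who bypasses the PACU, use all temperature data recorded over the monitored period and treat the absent PACU segment as missing, with a sensitivity analysis. Cutting the sum off at operating room exit would count the absent segment as zero hypothermia and lower that child's value.

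The cost is a change of wording and continued follow-up of children who are already inpatients. No larger sample is needed and clinical care does not change. The small downside is that some recovery scores and PACU temperature segments will be missing for children who stay intubated or sedated.

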### Intervention

2.4.

A total of 400 children will be randomly assigned to the active warming strategies group and the control group. The specific warming measures are as follows.

**Active warming strategies group (Group A):** Details about the active warming strategy are mainly described in Figure 3, which was carried out in a total of three locations, including the preoperative waiting room, the operating room and the postanaesthesia care unit (PACU). In the preoperative waiting room, pre-warming is mainly carried out using a forced-air warming blanket (40°C). If the child's body temperature is <36°C or subjectively feels cold, we further raise the temperature of the forced-air warming blanket and the temperature of the waiting room. Active warming measures in the operating room are to maintain the forced-air warming blanket at 40°C, the infusion equipment at 37°C, the body cavity lavage liquid at 38°C and the operating room temperature at 24°C. Active warming measures in the PACU are to maintain the forced-air warming blanket at 40°C, the infusion equipment at 37°C and the room temperature at 24°C. Real-time temperature monitoring will be maintained throughout the whole process. The nasopharyngeal core temperature will be monitored additionally for correction after anaesthesia induction and before awakening. All active warming measures will be discontinued on exit from the PACU.

**Figure 3 F3:**
[figure not shown]
Active warming strategies process.

**Control group (Group C):** Routine passive warming measures will be used in the perioperative period. Children will be covered in insulation layers from entering the preoperative waiting room to leaving the PACU. In the preoperative waiting room, the children will still use a warming blanket but not heated forced air and not raise the room temperature. In the operating room, the warming blanket is not heated and the rest of the warming measures, including the infusion equipment, the body cavity lavage liquid, and the temperature of the operating room, is at the discretion of the anaesthesiologist in charge. In the PACU, the warming blanket is also not heated and the rest of the warming measures, including the infusion equipment, and the temperature of the operating room, is at the discretion of the anaesthesiologist in charge. Similarly, real-time temperature monitoring will be maintained throughout the whole process. The nasopharyngeal core temperature will be monitored additionally for correction after anaesthesia induction and before awakening. If the children's temperature is <35°C throughout the perioperative period, regulations for body temperature protection will be enforced as described below.

**Regulations for body temperature protection:**
(1)If the core temperature of children in the two groups is <35°C, the active warming measures will be forced to start, or the warming level will be improved to avoid hypothermia.(2)If the children in Group A complain that they are hot, or the body temperature >37.5°C, the temperature of the forced-air warming blanket will be adjusted down until the children feel comfortable, or the body temperature is ≤37.5°C.In addition, the intervention measures involved in this study are routine clinical treatments, with little risk. It is expected that no damage will be caused to the participants, and there is no relevant compensation agreement. Children will be monitored routinely throughout the perioperative period and if there are serious adverse events related to this study during the study, such as cardiac arrest caused by severe abnormal body temperatures, they will be reported immediately to the PI and IRB by the anaesthesiologist in charge to break the blinding or terminate the study as appropriate.

